**Methods:**

The aim of this study is to adapt the implementation fidelity framework developed by Keith et al. and apply it to the intervention implemented in phase 1 of the Getting Better at Chronic Care in North Queensland study. The objectives are to quantify the level of implementation fidelity achieved during phase 1 of the study, measure the association between implementation fidelity and health outcomes and to explore the features of the primary health care system that contributed to improved health outcomes. A convergent parallel mixed methods study design will be used to develop a process for assessing implementation fidelity. Information collected via a questionnaire and routine data generated during phase 1 of the study will be used to explain the context for the intervention in each site and develop an implementation fidelity score for each component of the intervention. A weighting will be applied to each component of the intervention to calculate the overall implementation score for each participating community. Statistical analysis will assess the level of association between implementation fidelity scores and health outcomes.

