## Methods/design

The aim of this study is to adapt the implementation fidelity framework developed by Keith et al. and apply it to the communities that participated in phase 1 of the Getting Better at Chronic Care in North Queensland (GBACC) study. The GBACC study was a cluster randomised control trial (RCT)of intensive case management by Indigenous Health Workers of people with complex chronic disease care needs [26]. The primary outcome measure was reduction in HbA1c over 18 month and there were a range of secondary measures including improvement in clinical process measures and hospital avoidance for ambulatory sensitive chronic conditions. The study produced modest results and a possible reason for this is implementation failure of the intervention. This study will quantify the level of implementation fidelity achieved during phase 1 of the GBACC study and investigate the features of the primary health care system that contributed to successful improvement in clinical measures and hospital avoidance for ambulatory sensitive conditions.

The objectives of the study are to:Investigate the features of primary health care service models that contribute to intervention effectiveness for chronic disease care of Indigenous patients and identify if they are present in the context of health services participating in the GBACC study.Assess the level of implementation fidelity achieved for each component of the intervention in each community.Measure the level of implementation fidelity achieved in each communityDetermine if there is any association between implementation fidelity and health outcomes as measured by HbA1c and preventable hospitalisation for diabetes related conditions for communities in the GBACC study.

The study has approval from the Far North Queensland Human Resource Ethics Committee (HREC), University of Queensland HREC and the University of South Australia HREC.

A convergent parallel mixed methods design will be used to develop the measures for assessing implementation fidelity for each component of the intervention implemented during phase 1 of the study. The study will be executed in three stages using a model adapted from Carrol (2007 and Keith (2010). The analysis will use routine data generated by the GBACC study, clinical data collected to measure the outcome from the RCT and additional information collected via a questionnaire to describe the health service context in which the study occurred. The model is illustrated in Fig. 1.

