### Stage 3: Assessment of intervention effectiveness

The objective of stage 3 is to assess the impact of the program by looking at the association between the implementation fidelity score and outcome effectiveness. The aim is to determine if it is possible to predict outcome effectiveness based on the features of the PHC system. Intervention effectiveness (i.e implementation fidelity score for each component) is the independent variable and avoidable hospitalisations and service utilisation is the dependent variable.

Figure 3 provides a summary of the study design to assess implementation fidelity of phase 1 of the GBACC study.

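### The Stage 3 dependent variables do not match the fourth objective: HbA1c is left out, service utilisation is added, and the diabetes-related limit on hospitalisation is not repeated

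*Protocol article*

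**What the plan says.** Methods/design in the protocol article describes the parent trial: "The primary outcome measure was reduction in HbA1c over 18 month", with secondary measures that include clinical process measures and hospital avoidance for ambulatory sensitive conditions. It then gives the reason for the present study: "The study produced modest results and a possible reason for this is implementation failure of the intervention".

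The fourth objective in the same section is to look for an "association between implementation fidelity and health outcomes as measured by HbA1c and preventable hospitalisation for diabetes related conditions". Among its data sources the section lists "clinical data collected to measure the outcome from the RCT".

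Stage 3 (Assessment of intervention effectiveness) sets out the association analysis. On one side, "Intervention effectiveness (i.e implementation fidelity score for each component) is the independent variable"; on the other, "avoidable hospitalisations and service utilisation is the dependent variable". HbA1c is not mentioned in that section. The Methods paragraph of the abstract is neutral: "Statistical analysis will assess the level of association between implementation fidelity scores and health outcomes".

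**The concern.** An objective and the analysis meant to serve it should name the same outcomes. Here they do not, and no text in the article explains the difference. If the analysts follow Stage 3, the HbA1c part of the fourth objective is not addressed, and the implementation-failure explanation is not examined on the RCT's primary outcome. If they follow the objective, they depart from the one sentence that defines the dependent variable.

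The timing adds to this. The RCT results were already known when the article was written, since it calls them modest. With two outcome lists on record, either could later be reported as the planned one. Fixing the outcome list in advance is one of the main purposes of publishing a protocol.

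**Working it through.** No arithmetic bears on this point. The article states no sample size, event count or power for the association analysis, and the claim needs none. The check is a comparison of the two outcome lists, with the description of the RCT as background.

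| Outcome | RCT (Methods/design) | Fourth objective (Methods/design) | Stage 3 dependent variable |
|---|---|---|---|
| HbA1c | Primary, reduction over 18 months | Yes | No |
| Hospitalisation | Secondary, ambulatory sensitive conditions | Yes, preventable and diabetes-related | Yes, avoidable, with no condition named |
| Service utilisation | Not named as such | No | Yes |

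1. **Overlap.** The objective has two outcomes and Stage 3 has two. Only hospitalisation is in both.
2. **Dropped.** HbA1c is in the objective and not in Stage 3.
3. **Added.** Service utilisation is in Stage 3 and not in the objective. It is not defined and no reason is given for it.
4. **Altered.** The objective limits hospitalisation to diabetes-related conditions. Stage 3 does not repeat that limit, so its wording could equally mean the RCT's secondary outcome, which is worded in terms of ambulatory sensitive conditions.
5. **Does other text settle it?** The abstract refers only to health outcomes and neither names nor excludes HbA1c. The opening of Stage 3 speaks of outcome effectiveness in general terms. The list of data sources implies that HbA1c will be at hand but does not assign it to an analysis.
6. **Is this a detail left to a fuller document?** No. The article states the dependent variable, and that statement disagrees with its own objective. A statistical analysis plan or full protocol could resolve the conflict only by departing from one of the two published statements.

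**The case against.** The strongest reply is that a single sentence in Stage 3 should not override the rest of the article. The objective names HbA1c, the RCT outcome data are listed as a source, and the abstract promises an analysis of health outcomes. Figures 1 to 3 are not available here, and Stage 3 refers to Figure 3 as its summary, so a figure may list HbA1c. A drafting slip is then the likely explanation. This stands as an account of how the mismatch arose and it limits how much can be concluded. It does not remove the mismatch: even if a figure lists HbA1c, the two pieces of text still disagree.

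A reader might go further and infer any of the following, none of which the documents support.

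- *The study cannot say whether fidelity explains the RCT result.* That is too strong. Stage 3 as specified does not test HbA1c, but the article shows the intention and the data to do so. The modest results are also not attributed to HbA1c alone; the sentence follows a list that includes secondary outcomes.
- *HbA1c must be the primary dependent variable.* The objective names it first but sets no order of importance. Its rank in the RCT does not fix its rank here.
- *Hospitalisation is the weaker outcome because admissions are sparse and admission practice differs between communities.* The article says neither. Its Background compares rural and remote access with urban access, not one study community with another. Any figures for precision would rest wholly on assumed site sizes, rates and standard deviations.

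It is also fair to say that adding HbA1c will not make Stage 3 a decisive test. The service context questionnaire covers six intervention sites and scores are aggregated by community. If those six sites were the units of analysis, a two-sided 5% test of a correlation would have 4 degrees of freedom and a critical t of 2.776, so |r| would have to exceed 2.776/√(2.776² + 4) = 0.81. That tempers what the repair can deliver. It is no reason to leave the outcome lists in conflict.

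**Conclusion.** The point holds as an inconsistency within the current text. One of the two outcomes in the fourth objective has no analysis in Stage 3 as specified, one Stage 3 variable has no counterpart in the objective, and the single shared outcome is described in two ways. Part of the objective would go untested if Stage 3 were followed literally.

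This rests on reading the Stage 3 sentence as the specification of the association analysis, which is how it presents itself, and on the figures not being visible. It does not rest on any numerical assumption. It does not show that HbA1c was deliberately excluded, that the study as a whole is unable to address the RCT's findings, or that HbA1c should rank above hospitalisation. The mismatch should be corrected because it concerns the outcome set of the main quantitative analysis, and correcting it is easy.

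**What to change.** Rewrite the Stage 3 sentence so that it matches the fourth objective:

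- name two dependent variables: HbA1c change over 18 months, defined as in the RCT, and preventable hospitalisation for diabetes-related conditions;
- either label service utilisation as an additional outcome, with a definition and a reason, or remove it;
- if Figure 3 or any fuller protocol or analysis plan lists outcomes, bring that list into line.

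No ranking of HbA1c over hospitalisation is needed for consistency. If the investigators want one, they should state it as their own choice before the association analysis is run.

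The cost is one sentence and one further analysis. The RCT outcome data are already among the listed sources, so the article implies no new data collection.

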**Fig. 3 Fig3:**
[figure not shown]
Study design Implementation fidelity of GBACC study

## Discussion

Health services research seeks to find solutions to social and technical problems to improve health outcomes. Health services research is more complex than scientific research alone because it deals with societal problems in health care. In the Indigenous health setting the problems being addressed are often considered ‘wicked problems. That is the setting is complex, and there are many different views on the causes of poor indigenous health (the problem), the mission to solve problems is not always clear and there is not one agreed solution to the problem [27]. RCTs that use a mixed methods design provide more evidence and insight into the ‘societal’ issues to explain the outcomes achieved from RCT. However gaps often remain in our understanding of the scope of implementation that occurred and the impact that different components of an intervention had on outcomes. The development of a methodology for assessing implementation fidelity in the context of Indigenous primary health care health setting will help address some of the barriers identified with the translation of research into practice [15, 28] and produce better evidence about factors contributing or preventing successful implementation of programs in the research and real world setting.

## Abbreviations

GBACC: Getting better at chronic care in North Queensland study
HREC: Human Research Ethics Committee
RCT: Randomised control trial.
